## Abstract

**Purpose:**

In the paediatric age group, the overall degree of evidence regarding decompressive craniectomy (DC) and cranioplasty is low, whereas in adults, randomised controlled trials and prospective multicentre registries are available. To improve the evidence-based treatment of children, a consensus was reached to establish a prospective registry under the auspices of the European Society for Pediatric Neurosurgery (ESPN).

**Methods:**

This international multicentre prospective registry is aimed at collecting information on the indication, timing, technique and outcome of DC and cranioplasty in children. The registry will enrol patients ≤ 16 years of age at the time of surgery, irrespective of the underlying medical condition. The study design comprises four obligatory entry points as a core dataset, with an unlimited number of further follow-up entry points to allow documentation until adolescence or adulthood. Study centres should commit to complete data entry and long-term follow-up.

**Results:**

Data collection will be performed via a web-based portal (homepage: www.pedccr.com) in a central anonymised database after local ethics board approval. An ESPN steering committee will monitor the project’s progress, coordinate analyses of data and presentation of results at conferences and in publications on behalf of the study group.

**Conclusion:**

The registry aims to define predictors for optimal medical care and patient-centred treatment outcomes. The ultimate goal of the registry is to generate results that are so relevant to be directly transferred into clinical practice to enhance treatment protocols.

## Introduction

Decompressive craniectomy (DC) is part of the armamentarium to control critically raised intracranial pressure (ICP) occurring at different stages after severe cerebral insults [1] : Primary DC is used to treat patients with significant space-occupying lesions, in whom the risk of evolving brain edema is high. Secondary or delayed DC is usually considered as a final step if intracranial hypertension becomes refractory to conservative measures. In addition to the implications of primary and secondary brain injury itself, the limitations, inherent risks and complications of DC and also of subsequent cranioplasty have to be taken into account.

Looking at the adult age group, several studies with high-quality methodology have been or are being conducted: A randomised controlled trial (RCT) investigating the role of primary DC (RESCUE-ASDH) has finished enrolment and the final results are not yet published (ISRCTN87370545). Concerning secondary DC for refractory intracranial hypertension (> 25 mmHg) due to severe traumatic brain injury (TBI), the RESCUEicp trial indicated a lower mortality compared to conservative management [2]. The similar DECRA trial had a lower ICP threshold (> 20 mmHg) and demonstrated reduced mortality but more unfavourable outcomes after DC [3]. For malignant ischemic stroke, several RCTs (including HAMLET, DECIMAL, DESTINY I and II) proved a significant reduction of mortality, although DC renders a relevant subgroup with moderately severe disability [4–7].

In contrast, such high-level evidence is not available in the paediatric age group, where the large majority of previous publications are retrospective and monocentric [8–18]. For a recent review on DC in paediatric TBI, Ardissino et al. screened 212 studies, but only 12 ultimately qualified for systematic comparison [19]. The authors concluded that DC reduces mortality and may improve functional outcome, but they also highlighted significant knowledge gaps. Results for DC in paediatric ischemic stroke are limited to case series and anecdotal case reports [20].

Regarding cranioplasty, the level of evidence is low for all age groups. Klieverik et al. recently screened 393 publications on paediatric cranioplasty and ultimately included 24 articles in their systematic review [21]. They concluded that both autologous and alloplastic cranioplasty appeared to be associated with relevant complication rates, with the problem of aseptic bone flap resorption having a pronounced impact on the paediatric cohort. Beyond this, no reliable conclusions were possible and the authors emphasised the relevance of large prospective cohort studies. To improve the evidence base in adults, two prospective multicentre registries are actively recruiting patients ≥ 18 years of age in Europe (UKCRR in the UK and GCRR in Germany, Austria and Switzerland) [22, 23].

The recent efforts of both Ardissino et al. and Klieverik et al. highlight the problems encountered in paediatric DC and cranioplasty [19, 21] : The pooling of published results is hindered by heterogeneous data elements and by missing information. Few studies provide long-term information spanning craniectomy and cranioplasty, although both operations are closely related and relevant to the overall morbidity and outcome of individual patients. If we attempt to fill these evidence gaps with extrapolation of study results obtained in the adult age group, there is a significant caveat: Highly relevant differences in anatomy and physiology are described between adults and children and even within the paediatric age spectrum [24, 25]. Additionally, a fixed point of outcome assessment as used in adults (in virtually all RCTs after 6 and/or 12 months) does not adequately reflect the impact of injuries and treatments on the developing child’s brain. Children require longitudinal observation over many years with age-adjusted outcome measures.

To this point, it should have become clear that the field of paediatric DC and cranioplasty requires significant research activity. However, to further justify such efforts, the relevance of the field has to be taken into account as well. In the paediatric age group, the main cause of severe acute primary and secondary brain injury with consecutive intracranial hypertension and need for decompressive craniectomy (and thus later cranioplasty) is TBI. Therefore, the best epidemiological and health-economic data is available for this condition: 30% of all TBI cases occur in patients under the age of 16, of which approximately 10% suffer moderate or severe TBI [26]. The financial burden of TBI is significant, with estimated annual costs for TBI-related hospitalisation of children in the USA of more than $ 1 billion [27]. With regard to medical outcomes, it is assumed that 30% of children do not survive severe TBI despite DC [14, 28]. Among survivors a good outcome can be expected in 60–90% depending on the type of initial cerebral insult [28, 29]. In addition to the sequelae of the insult itself, the risks of DC and cranioplasty (especially CSF disorders, infections and resorption of autologous bone flaps with the need for revision surgery) need to be taken into account [13, 30–34]. The field is therefore highly relevant for the individual child and, not least due to associated health-care costs, also to society.

The initial proposal for this study was presented at the ESPN Consensus Conference 2019 in Paris. At this conference, a consensus was reached to establish a multicentric registry under the auspices of ESPN. Achieving optimal outcomes after severe insults to the child’s brain is of utmost importance and the ESPN pedCCR will significantly contribute towards this aim.

## Aims and objectives

After reaching consensus to establish a multicentre, prospective, registry under the auspices of ESPN, an initial international steering committee was formed to formulate the study goals and generate a proposal for a study protocol, which was subsequently ratified by the ESPN board.

The primary objective of this study is a detailed systematic assessment of DC and cranioplasty in children (defined as patients ≤ 16 years of age at the time of surgery) with regard to indication, timing, technique and outcomes, irrespective of underlying disease and with a minimum follow-up of 24 months after cranioplasty. The secondary objective is the comparison of treatment strategies and identification of predictors for optimal outcomes of DC and cranioplasty. This study will generate an international multicentric, prospectively collected data set to achieve these objectives.

Such systematic and high-quality data collection and analysis will improve the evidence base and thus medical care in several specific aspects. The concept of the study is characterised by patient orientation: Based on a large, prospective patient series, we aim for identifying risk factors as well as optimal and suboptimal approaches. This effort may ultimately reduce the complication rate, thereby increasing patient safety and optimizing outcome. The study protocol explicitly includes the long-term course and health-related quality of life (using KIDSCREEN-10) in age-dependent self or external assessment, in addition to the King’s Outcome Scale for Childhood Head Injury (KOSCHI) [35, 36]. The latter scale is validated for TBI, but can be applied to other conditions similar to the Glasgow Outcome Scale.

A systematic analysis and comparison of different cranioplasty materials and techniques will deliver further knowledge in order to optimise quality of care and cost-effectiveness in this critical phase after TBI, as cranioplasty carries significant short- and long-term risks in children [34]. Ultimately, based on the data collected, revision surgery could be avoided and implants with the best cost–benefit ratio could be identified. Additionally, the optimal timing of cranioplasty will be analysed, as there is currently conflicting data on early versus delayed cranial reconstruction [37–40]. A further strength of the registry is its focus on specific technical details from a paediatric neurosurgical perspective, which are often impossible to be reconstructed retrospectively from operation notes.

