### Study design

This is a multicentre, prospective, registry. Patients ≤ 16 years of age at the time of surgery can be included after informed consent as detailed below, irrespective of underlying disease (i.e. indication for DC). In surviving patients, the study centres are committed to contributing data on subsequent cranioplasty as well as a minimum follow-up of 24 months after cranioplasty (Fig. 1). Further follow-up until adolescence or adulthood is encouraged.

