**Fig. 1 Fig1:**
[figure not shown]
Illustration of the study design, with 4 obligatory data entry points for a complete core data set

The criteria applying for patient enrolment into the registry were kept simple as a result of the low incidence of DC in children and to actively encourage recruitment (Table 1).

**Table 1 Tab1:** Overview of inclusion and exclusion criteria

Inclusion criteria	Exclusion criteria
- Age ≤ 16 years at the time of surgery	- Cranioplasty for conditions other than DC (e.g. congenital skull defects)
- Any type of underlying cerebral insult	
- Informed consent obtained	
- Ability to provide follow-up of at least 24 months after cranioplasty	

Based on retrospective data and an exploratory review of the literature, we estimate an annual recruitment of 2 to 5 patients per centre. The experience of the German Cranioplasty Registry for adult patients (GCRR) has shown that approximately 10 national centres can be expected to participate, depending on the size of the country [22]. Sample size justification is based on a minimal assumption of 20 contributing centres for the ESPN pedCCR, with mean enrolment of 3.5 patients per year. The registry could therefore have an annual recruitment of 70 patients.

Data entry will be web-based and the protocol is optimised towards efficiency and low resource requirements for the contributing centres in order to encourage active and lasting enrolment, complete data entries and sufficient follow-up. A complete minimal data set for a patient surviving after DC would include four data entry points, i.e. forms for DC Module, Cranioplasty Module and two Routine Follow-up Modules at 12 and 24 months after cranioplasty, respectively (Fig. 1). The data elements for each module are partially based on the National Institute of Neurological Disorders and Stroke (NINDS) Common Data Elements (https://commondataelements.ninds.gov). Additionally, several validated scores and measures are explicitly or implicitly contained within the forms. The forms for each module are outlined below:

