### Decompressive craniectomy module

48 itemsPaediatric GCS prior to DC and at discharge or day 30 after DC [41]Paediatric Risk of Mortality Score (PRISM) within 4 h after admission [42]Rotterdam CT Score [43]KOSCHI at discharge or day 30 after DC [35]

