**Fig. 2 Fig2:**
[figure not shown]
Representative screen shots of the pedCCR database — **A** homepage (homepage: www.pedccr.com) and **B** data entry form for DC

Patients will be pseudonymised (consecutive numbers) locally by the respective centre. The central data collection will then be done anonymously, i.e. the central database itself does not contain any identifying patient information and the pseudonymisation key will be securely kept at the local centre.

As this is a prospective registry without a limited study period, data collection will be ongoing and no endpoints were predefined. Regular audits will be performed to ensure data quality and integrity. Data analysis will be performed with descriptive statistics. Based on results from the previous literature, the following statistical assumptions regarding relevant clinical variables were made: 30-day-complication rate after DC — 40%; good outcome after DC — 50%; mortality after DC — 30% and autologous bone flap resorption rate — 80%. With the aim of a confidence level of 90% and an error margin of less than ± 10%, an analysis will be carried out for *N* = 100 included cases. To compare the complication rate between autologous versus allogeneic cranioplasty, an evaluation of *N* = 150 cases per cranioplasty modality will be carried out in view of the complication rates from the literature of 33% versus 14%.

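### Long-term KOSCHI and KIDSCREEN-10 forms are counted from cranioplasty, so a descriptive early-versus-delayed comparison would mix timing with time since injury and survival to surgery

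*Protocol article*

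**What the plan says.** All references are to the Protocol article.

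- **The question.** Aims and objectives commits the registry to a timing analysis: "the optimal timing of cranioplasty will be analysed, as there is currently conflicting data on early versus delayed cranial reconstruction". The same section puts timing in the primary objective and the comparison of treatment strategies in the secondary one.
- **The clock.** The primary objective is framed "with a minimum follow-up of 24 months after cranioplasty". Study design lists the obligatory forms as one for DC, one for cranioplasty, and "two Routine Follow-up Modules at 12 and 24 months after cranioplasty, respectively". KOSCHI and KIDSCREEN-10 are on the routine follow-up form.
- **Assessments tied to DC.** The DC module has "KOSCHI at discharge or day 30 after DC", and Paediatric GCS at the same point. No later assessment has a fixed time since DC. Further follow-up is encouraged without set times.
- **Assessments around cranioplasty.** The cranioplasty module takes KOSCHI before the operation and again at discharge or day 30. KIDSCREEN-10 is taken before the operation only.
- **Who contributes.** "In surviving patients, the study centres are committed to contributing data on subsequent cranioplasty". Table 1 also lists as an inclusion criterion "Ability to provide follow-up of at least 24 months after cranioplasty". The assumptions under Data management and statistical analysis include "mortality after DC — 30" per cent.
- **Method.** "Data analysis will be performed with descriptive statistics". The same section says that endpoints were not fixed in advance.

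**The concern.** In a timing analysis the exposure is the wait from DC to cranioplasty. If the outcome is read 12 or 24 months after cranioplasty, a child who waited longer is also assessed longer after the brain insult, with more time to recover and grow. The article's own Introduction argues that children need observation over many years with age-adjusted measures, so functional and quality-of-life scores should be expected to move with time since injury and with age. A table of scores by early and delayed groups cannot tell an effect of timing from an effect of elapsed time.

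The second issue is selection. A child enters the comparison only on reaching cranioplasty, and reaching a late one requires longer survival. Children who die while waiting belong to neither group, although their deaths may bear on whether waiting is wise.

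At stake is a question that the article gives as a reason for the registry. An answer that carries these two distortions would add to the conflicting evidence.

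**Working it through.** The article gives no sample size, precision target or effect for the timing question, so there is no figure to reproduce. Its N = 100 (single proportions) and 150 per group (autologous versus allogeneic) serve other purposes.

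**1. Time since DC at the obligatory forms**

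Inputs: form times v = 12 and 24 months after cranioplasty (Study design). The interval I from DC to cranioplasty is not given, and the article does not define early or delayed, so the pairs below are assumed.

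Formula: time since DC = I + v.

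| Assumed I, early v delayed (months) | 12-month form, months since DC | 24-month form, months since DC | Gap (months) |
|---|---|---|---|
| 1 v 3 | 13 v 15 | 25 v 27 | 2 |
| 2 v 6 | 14 v 18 | 26 v 30 | 4 |
| 2 v 8 | 14 v 20 | 26 v 32 | 6 |
| 3 v 12 | 15 v 24 | 27 v 36 | 9 |

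The gap is always the difference in I, whatever v is. A later form from the same schedule does not shrink it.

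**2. Why adjustment at one form does not help**

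At the 12-month form, time since DC is I + 12. Exposure and elapsed time differ by a constant, so a regression at that form cannot separate them, apart from small departures from the nominal visit date. Separation needs scores from several times per child, so that operated and not-yet-operated children can be compared at similar times since DC. For a child operated on at 8 months, the obligatory forms give KOSCHI soon after DC, at about 8 months (before cranioplasty), at discharge or day 30 after it (at the latest about 9 months), and at 20 and 32 months. These can be modelled as a trajectory.

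**3. Change from the pre-cranioplasty score**

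This is available but does not remove the problem. With I = 2 and 8, the 12-month change covers months 2 to 14 in one group and 8 to 20 in the other. If recovery slows with time, the earlier window shows more gain whatever the effect of timing. The raw 12-month score would lean the other way.

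**4. Who reaches the comparison**

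If all deaths in the stated 30% mortality came before cranioplasty, 100 × (1 − 0.30) = 70 of 100 children would reach it. The article does not say when deaths occur. Only deaths between the early and the delayed operation times separate the groups.

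Formula: share of waiting children who die in a window of d months = 1 − exp(−h × d), with an assumed constant monthly hazard h of 0.5% to 2%.

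From month 2 to month 8, d = 6:
- h = 0.5%: 1 − exp(−0.03) = 1 − 0.970 = 3.0%
- h = 2%: 1 − exp(−0.12) = 1 − 0.887 = 11.3%

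These children would be in neither group. The hazard is an illustration only.

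**The case against.** **The article never says which outcomes the timing analysis will use.** This is correct. A reader might infer that the plan has fixed the 12- and 24-month scores as the timing endpoint. It has not: no endpoint is assigned, and a DC-based clock is not ruled out. An analysis plan that is not shown could settle time zero and the model. What stands is narrower. The comparison is promised, the obligatory schedule offers no other long-term functional outcome, and the stated method is descriptive.

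**The cranioplasty clock is natural for much of the question.** Also correct. The text around the timing sentence is about cranioplasty risks, revision and implants, and complications also come through incident reports. For infection, resorption and revision, the operation is the right origin. The point is confined to function, quality of life and survival.

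**This is not immortal-time bias.** A reader might use that label. While follow-up starts at cranioplasty, the wait is not counted as follow-up, so the problem is selection of children who reached surgery. Immortal time arises if the clock moves to DC and children are classified by their eventual timing. The fix must therefore use a time-dependent exposure or a landmark.

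**Size and direction are not established.** A reader might infer a false advantage for delay. If the share with a good score rose by an assumed 0.5 to 2 points a month, 6 months would give 3 to 12 points. The article supplies no such slope. Its ±10% margin is for single proportions and is no yardstick here. If more severely affected children are operated on later, confounding would work against delay.

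**Conclusion.** The concern holds in a limited form. If the timing question is answered descriptively from the obligatory 12- or 24-month KOSCHI and KIDSCREEN-10 forms, early and delayed groups will differ in time since DC by exactly their difference in waiting time: 2 to 9 months under the assumed intervals, for example 14 against 20 months for waits of 2 and 8. Only children who survived to cranioplasty will be compared. The size and net direction of the resulting bias are unknown.

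This rests on two readings: that function or quality of life will be among the timing outcomes, which the article implies by its choice of measures but does not state, and that no other method is specified in a document not shown. It does not touch complications of the cranioplasty itself. The point is a cheap improvement and not a flaw that invalidates the registry.

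**What to change.** Add a short statement to Aims and objectives and to Data management and statistical analysis, limited to timing analyses with functional, quality-of-life or survival outcomes:

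1. Set time zero at DC and model cranioplasty as a time-dependent exposure. Alternatively, choose a landmark after DC and include every child alive at that time, classified as already operated on or not yet operated on.
2. Model all recorded KOSCHI scores (after DC, before and after cranioplasty, at 12 and 24 months, and any further follow-up) and the available KIDSCREEN-10 scores as repeated measures by time since DC.
3. Adjust for age, type of insult and early post-DC severity (GCS and KOSCHI at discharge or day 30).
4. Keep cranioplasty as the origin for infection, flap resorption and revision.

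Cost: no new form, but a somewhat more complex analysis than descriptive tables. A landmark leaves out children who died before it. KIDSCREEN-10 starts only before cranioplasty, so its trajectory will be thinner than that of KOSCHI. The fix assumes that the dates of DC, cranioplasty and each assessment are recorded. The item lists are not shown, so this should be confirmed.

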### Study design

This is a multicentre, prospective, registry. Patients ≤ 16 years of age at the time of surgery can be included after informed consent as detailed below, irrespective of underlying disease (i.e. indication for DC). In surviving patients, the study centres are committed to contributing data on subsequent cranioplasty as well as a minimum follow-up of 24 months after cranioplasty (Fig. 1). Further follow-up until adolescence or adulthood is encouraged.

